## 8. Data management

Data will be retracted from the repeatedly saved analytics. During the pilot study syntax/algorithms for data output were developed, tested, and refined. Several datasets will be constructed as Excel-files and merged to one single file (master dataset). Merging data (based on subject-ID) and resolving data queries will be made by two researchers in dialogue with the data manager from the investigator site (LongLife Active). Database cleaning, rectifying errors and resolving issues will be made by two researchers in collaboration with the investigators.

The research study is managed as a separate module of the system, which enables automatic and anonymous communication with the research subjects, and safe data transfer limited to the research purposes on an individual- and group level without sharing any personally identifiable information. Transfer of data from the server to the principal investigator will be made through a regulated and monitored web platform with obligatory electronic identification for access.

At Sophiahemmet University data will be stored at Sunet Drive for Sophiahemmet University.

## 9. Amendments to the CIP

The CIP is saved at OneDrive for Sophiahemmet University and the latest version is available to the investigators and the research group as a shared document. Amendments to the CIP are as made as comments in the document. When the CIP is updated, old versions will be saved, and the amendments will be logged in the old version as well as in a separate document (CIP log).

## 10. Deviations from the clinical investigation plan

Any deviations from the CIP will be documented in a log (a separate Word-file, CIP log) along with reasons to the deviations and date. When the CIP is updated, old versions will be saved.

## 11. Device accountability

Access to the investigated medical device will be controlled using electronic identification (BankID). Subjects in the control group will be excluded if they answer they are using some digital support for behavior change. In addition, a comparison of names and email addresses it will be made to check that the control subjects are not using the investigated medical device.

## 12. Statements of compliance

Etiska överväganden enligt Annex A12

## 13. Informed consent process

Individuals who sign up for the digital service LongLife Active from October 2023 (or as soon as ethical approval is obtained) will be informed about the research study (informed consent in supplement 5a) and invited to consent for data extraction in the app. Controls will be recruited through social media and through large companies and will be sent the detailed information by email (supplement 5b). Control subjects consent in the survey tool before starting to answer the questionnaire.

## 14. Adverse events, adverse effects, and device deficiencies

Alerts and report functions are built into the system to alarm excessive habits and low well-being score. The quality manager and health coaches manage and monitor alerts and inappropriate posts in the community. A Monitoring plan has been developed which covers processes of all risk management activities and security measures based on the risk assessment including operative guidelines for LongLife Actives health coaches. The Quality manager is responsible for risk management and educates all stakeholders involved in risk management activities. Adverse events and issues that are arising are logged and discussed among the investigators and sponsor and are at first hand alleviated.

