## 2.2 Description of the device

The medical device to be investigated is a digital service aimed to support healthy habits and improve well-being among the general adult population. The digital service includes three core subjects:

1) a Healthy diet, 2) Physical activity, and 3) Mental balance.

The service includes tracking and self-monitoring of behaviors, goal setting, action planning, feedback and digital rewards, a database with food recipes, a database with exercises, inspiration and skills training webinars and articles, and an AI chat. Figure 1 illustrates the core functions of the service.

The included functions and applied behavior change techniques (BCTs) are presented in supplement 4, *Overview functions and BCTs*. Users may sign up for three levels of memberships. The first level (Basic) includes the beforementioned functions, the second level (Standard) also includes a community for social support, and the third level of subscription (Premium) includes a community and the possibility for private health consultations. The number of private health consultations is 3 for a 3 months subscription, 4 for a 6 months subscription, and 6 for a 12 months subscription.

Figure 1. Print screens from the device showing the core intervention components.

The digital service is assisted by artificial intelligence to direct the support to the individual timely and based on each user's needs, motivation, preferences, experiences, opportunities, and capabilities. A literature review undertaken during the development phase showed users of digital services wish for interface design and reminders to be customizable, and that the service is integrated with other services (such as shopping lists) (2). These are aspects that have been regarded to keep engagement over time. With a straightforward design, pictures, and short video instructions the service is customized for people with low skills in the Swedish language or with low digital literacy. Hence, no training or previous experience in digital health services is needed before using

the device. An AI chat is included as a core function to offer individualized support and guidance concerning the user's action plan and goals. Phrases and constructed dialogues of the chat have been developed by health professionals with expertise and experience in health coaching and motivational interviewing.

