### 4.2 Anticipated adverse device effects

Adverse effects of digital support for behavior change are not obvious, and none have been reported in the scientific literature as far as we are aware. A systematic review including 113 RCTs investigating healthy diet and physical activity counselling reporting on adverse effects found no evidence for greater harm in the intervention versus the control group (33). Nevertheless, there are some identified concerns associated with the use of digital services for behavior change. The main risks that concern end-users are related to data security and confidentiality, reliability of the device,

and trustworthiness of the manufacturer (2, 23). Demotivation, self-confidence, self-consciousness, factors interrupting tracking, and data inaccuracy are common reasons for discontinued use (14).

Additional risks are increased screen time, perceived stress and excessive exercise and eating behaviors, potentially leading to orthorexia, and eating disorders. Filling out forms about mental health status and lifestyle behaviors may give rise to anxiety and low self-esteem. Not reaching self-identified goals and lack of expected results may cause a feeling of failure and hopelessness. Chat groups may be used to harass other subjects and encouragement and feedback can be misunderstood by subjective interpretation. Ultimately, behavior change will improve clinical values (e.g. blood lipids, metabolic control, blood pressure, pain, and sleep). Individuals on medication would conceivably need to adjust the dose of medication. There is a risk for relapse in behavior change and to re-adjust the medication.

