## 6.4 Monitoring plan

In this project most of the procedures are built into the app and are made automatic. Questionnaires and reminders to answer the questionnaires will be pushed through the app and data will be retracted from the continuously saved analytics. Supplement 3 shows the Case Report Form with variables that will be extracted for each individual.

All data is pseudonymized and stored in a three-level categorized and double-encrypted server to ensure personal integrity and security. The research study is managed as a separate module of the system, which enables automatic and anonymous communication with the research subjects, and safe data transfer limited to the research purposes on an individual- and group level without sharing any personally identifiable information. Transfer of data from the server to the principal investigator will be made through a regulated and monitored web platform with obligatory electronic identification for access.

Time points for the specific questionnaires are shown in table 1. The time for pushing out questionnaires is programmed at start and controlled by the investigators.

Routines for documentation on adverse effects is described in the IB (supplement 3). All involved personnel: quality manager, health coaches, webinar hosts and else are introduced to the IB and trained in the documentation process.

The IB will be saved as an online file to make sure everyone has the latest version. Changes made to the IB are highlighted and logged at the last page. Before changes are made a version of the IB is saved, named with version number and date.

Parts of the monitoring reports will be published in scientific journals as a process evaluation describing implementation factors, reach and engagement.

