### 7.4 Sample size calculation

The endpoint well-being will be assessed using the WHO-5 Well-being Index (34). In our pilot study the mean score at baseline was 55. The instrument has to our knowledge not been applied on a general Swedish population. In Danish general population surveys, the mean WHO-5 score was 60-70 ( $sd=19.0-19.9$ ) (36, 47, 48). A change of 10-20 points in WHO-5 has been proposed as a clinically relevant change (36, 49). In up-scaled interventions 60% lower effects are expected (50). We therefore aim at a difference of 12 points in the score between intervention groups and control group as well as between baseline and 6 months. A fluctuation in well-being is considered normal (36), subjects with well-being score  $>70$  are not expected to improve and will be excluded from the analysis. In the pilot study 21% of participants reached 70 points at baseline.

Desirable sample size was calculated to detect an effect of 12 points (36, 51) based on the assumption of two-tailed testing, an alpha error  $\alpha=0.05$  and power  $1-\beta=0.90$  and  $sd=19.9$  (48). To detect a medium standardised effect size of 0.5 (Cohen's d) for the primary outcome well-being at 6 months a sample size of at least 25 subjects per group is recommended. Expected drop-out rate due to withdrawal and lost to follow-up at six months is 75 %. Based on the expected drop-out rates and on excluding 20% from the analysis due to baseline score  $>70$ , we need to recruit at least 500 subjects to assure 25 subjects in each intervention arm. In the control group we assume subjects to be excluded based on using a digital product for behavior change and strive to include 200 subjects.

The secondary outcomes are exploratory due to the person-centred design of the service. The subjects will set individual goals and possibly change goals during the intervention. Likewise, habits and behavior change are largely changeable due to circumstances. The current research is not immense enough to guide a decision for minimal expected effects when individual goals are set (e.g., reducing weekly servings of red meat). A larger sample size than what is required for the primary

endpoint well-being is desired. Similarly, the secondary analyses of mediating factors and responsiveness require a large sample size. We therefore aim to include 5000 subjects.

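### As described, adverse effects are captured passively through app alerts and service staff with no uniform scheduled question, so recorded harms could not be compared fairly across subscription levels, people who stopped, or controls

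*Protocol*

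**What the plan says.** Section 4.2 anticipates more screen time, stress, excessive exercise and eating that might progress to eating disorders, a sense of failure after missed goals, and harassment in chat groups. On medication it adds: "There is a risk for relapse in behavior change and to re-adjust the medication".

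Section 14 describes how harms come to light. The first route is automatic: "Alerts and report functions are built into the system to alarm excessive habits and low well-being score". The second is oversight by people working for the service: "The quality manager and health coaches manage and monitor alerts and inappropriate posts in the community". On what happens to an event once it is known, the section says: "Adverse events and issues that are arising are logged and discussed among the investigators and sponsor". Section 6.4 places the documentation routine in the Investigator's Brochure (supplement 3) and states: "All involved personnel: quality manager, health coaches, webinar hosts and else are introduced to the IB and trained in the documentation process".

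Section 2.2 sets contact by level. Basic has the core functions and Standard adds the community. At the top, "the third level of subscription (Premium) includes a community and the possibility for private health consultations", with 3, 4 or 6 consultations for a 3-, 6- or 12-month subscription.

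Table 1 (section 6.3.2) schedules WHO-5 at months 0, 1, 3, 6, 12, 18 and 24, and KEDS, OLBI and ISI at months 0, 3, 6, 12, 18 and 24. It has no adverse-effect row. Under section 13, controls consent and answer in a survey tool. Under section 15, intervention subjects contribute data for 25 months and controls for 7.

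**The concern.** An event that nobody asks about is recorded only if an alert fires, a member of staff notices it, or the person volunteers it. Those chances are not the same in every group. Premium users may meet a coach, Standard users post in a moderated community, Basic users have neither, and controls have no described contact beyond a survey. If harms are tabulated by group from such records, real differences in risk cannot be told apart from differences in being noticed.

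This matters because section 4.6 asserts that benefits outweigh risks, section 4.5 promises that residual risks will be monitored and analysed, and section 15 makes a large volume of complaints a reason to terminate. All three need harm data whose completeness is known.

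**Working it through.** There is no stated figure to reproduce: the protocol gives no adverse-event rate and no detection probability. The check is a comparison of text, with two small calculations.

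**Step 1. Routes by group, as described.**

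| Route | Basic | Standard | Premium | Stopped using the app | Controls |
|---|---|---|---|---|---|
| App alerts (section 14) | yes | yes | yes | not stated | none described |
| Monthly WHO-5 prompt (4.5) | yes | yes | yes | not stated | none described |
| Technical support and support chat (2.2, 6.3.2) | yes | yes | yes | not stated | none described |
| Webinars, with hosts trained to document (2.2, 6.4) | yes | yes | yes | not stated | none described |
| Community overseen by coaches (2.2, 4.5) | no | yes | yes | not stated | none described |
| Private consultations (2.2) | no | no | optional | not stated | none described |
| Scheduled questionnaires, no adverse-effect item in Table 1 | yes | yes | yes | invited, online (6.2.1) | well-being at least |

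The first four routes name no level. The difference between levels comes from the community and the coach. The questionnaires are the one channel that reaches all five columns.

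**Step 2. What the scheduled scales cover.** KEDS and OLBI follow stress and exhaustion, WHO-5 follows mood and well-being, and ISI follows sleep. As named, none targets excessive exercise or restrictive eating, harassment, or injury and health-care contact related to lifestyle change. Table 1 also has lifestyle measures, but as outcomes, and the step counts and dietary questions apply only to people who chose that goal.

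**Step 3. The low well-being alert as a harm signal.** The threshold is 50 or below (section 4.5). The pilot baseline mean was 55, and the Danish surveys gave an SD of 19.0 to 19.9 (section 7.4). Assuming normality and that this SD applies:

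- SD 19.9: z = (50 − 55)/19.9 = −0.25, and Φ(−0.25) ≈ 0.40.
- SD 19.0: z = (50 − 55)/19.0 = −0.26, and Φ(−0.26) ≈ 0.40.

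About 40% would be at or below the threshold before any exposure. On its own, the alert marks a state and not a worsening.

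**Step 4. Effect of unequal detection (all inputs assumed).** Recorded rate = true risk × detection probability, with the same true risk in every group.

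| True risk | Detection: Basic, Standard, Premium, controls | Recorded rates |
|---|---|---|
| 2% | 0.5, 0.6, 0.8, 0 | 1.0%, 1.2%, 1.6%, 0% |
| 5% | 0.5, 0.6, 0.8, 0 | 2.5%, 3.0%, 4.0%, 0% |
| 10% | 0.5, 0.6, 0.8, 0 | 5.0%, 6.0%, 8.0%, 0% |
| 5% | 0.2, 0.4, 0.8, 0 | 1.0%, 2.0%, 4.0%, 0% |

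If detection were equal across levels, the gradient between them would vanish.

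**Step 5. Observation time.** The windows are 25 and 7 months, and 25/7 ≈ 3.6. Raw counts over the whole study would differ between intervention and control even at equal monthly rates and equal detection.

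**The case against.** The strongest reply is that much of the relevant material is not in view. The Investigator's Brochure, the case report form and the Monitoring plan are all cited and not shown, and Table 1 is offered as an overview. A reader might infer that alerts and staff are the sole route. The protocol does not support that, and the case report form may already contain a harm item.

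A reader might also infer that surveillance ends when app use ends, and put the size of the gap at 75%. Section 6.2.1 invites people who stop to keep answering online; whether alerts or logging attach to those answers is simply not stated. The figure in section 7.4 is something else: "Expected drop-out rate due to withdrawal and lost to follow-up at six months is 75" per cent. That is loss from the study, not a rate of stopping use.

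Nor does it follow that Premium must look least safe. Four routes name no level, and consultations are optional: in the pilot, 20 of 50 active users had at least one coaching session. The pilot's statement that no adverse events were reported cannot be discounted because of a 30% response either. That figure belongs to the usability questionnaire at week 3, and the pilot also used running comments, interviews and focus groups.

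Two further points stand. Stress, mood and sleep are already measured on a fixed schedule, and well-being must be collected in controls for the primary comparison, so worsening on WHO-5 has a comparator to month 6. And no objective, hypothesis or analysis in sections 5 and 7 compares harm rates; some harms, such as harassment in the app's community, cannot arise in controls.

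These points narrow the concern without removing it. Staff documentation, however thorough, is not the same as asking every participant the same question at the same time.

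**Conclusion.** The concern holds in a limited form. The protocol describes no adverse-effect question asked identically, at the same time points, of all levels, people who stopped, and controls. The routes it does describe are passive, and staff and community contact rises with subscription level. Recorded harms would therefore partly reflect ascertainment and could not be compared fairly between those groups.

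The size is unknown. Under the assumed detection values above, equal true risks yield recorded rates that differ between Basic and Premium by a factor of 1.6 (0.8/0.5) to 4 (0.8/0.2), and a recorded rate of zero in controls. The direction is plausible, not certain. The conclusion assumes that the supplements not shown do not already supply a uniform item.

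A reader might take this as a flaw in a planned analysis. It is not one: no such analysis is planned. It limits what the study can say about harm, and a modest change is worth making.

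**What to change.** First check the case report form. Unless it already has one, add a short, identical adverse-effect item set for the harms that the existing scales do not target: excessive exercise or restrictive eating, harassment, and injury or health-care contact related to lifestyle change.

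- Ask it at months 3, 6, 12, 18 and 24 at every level, including the online version for people who have stopped.
- Ask controls the same items in their questionnaires up to month 6, omitting items that cannot apply to them.
- Report these solicited harms by group, with response rates, and restrict comparisons with controls to the shared period.
- Use WHO-5, KEDS, OLBI and ISI for deterioration in mood, stress and sleep instead of adding duplicate items.
- List alert- and staff-reported events separately as unsolicited.

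The cost is slightly longer forms and an update to the case report form, with no extra visits or staff. The items will not recover people lost to follow-up, so the response rates must be shown beside the harm rates.

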## 15. Suspension or premature termination of the clinical investigation

The intervention subjects are included in the research study and contributing with data until 25 months have passed since registration of the first activity, or until reporting a wish to withdraw. Control subjects are included in the research study and contributing with data until 7 months have passed since submitting the first questionnaire, or until reporting a wish to withdraw. Reasons to terminate the research study are if large quantities of complaints are made about the digital service or about the burden of answering questions, or if 5000 subjects are not reached within 5 years.

## 16. Publication policy

The research project will be part of a post doc project and integrated in two or more doctoral theses. Thus, the research findings will be disseminated through peer reviewed open access journals that are recognized and indexed in PubMed. The Vancouver guidelines by ICMJE will be followed to decide authorship order and be transparent of author contributions. Supplement 7 shows the planned studies and authorships that has been agreed upon.

The scientific results will also be disseminated through publishing in popular science journals and presentations at national and international conferences and seminars. At Sophiahemmet researchers collaborate very close with the marketing department when communicating with the wider society. The channels och types of information will be adjusted and focused to the target groups. Here we present at broad plan for channels.

### Dissemination to the population

The research group has established networks and channels for research dissemination to the population, e.g. newsletters and social media that will be used. The company providing the app will spread updated information through social media and newsletters. Users of the app will regularly be updated about the research progress through short articles, videos, and webinars at a page for the purpose within the app.

### Dissemination to politicians and practitioners

The results will be presented in scientific journals, professional journals and networks, through social media and through presentations at national and international conferences.

